**Fig. 1 Fig1:**
[figure not shown]
Flowchart of the OmegaROP-2 study

For mother-infant dyads born before 29 GA, screening will be performed in the Pathological Pregnancy Department. Screening will be carried out in the delivery room for patients delivering at full-term. First, the investigating physician provides the patient with information and answers questions about the research study’s purpose and requirements. They also specify the patient’s rights when participating in biomedical research and verify the eligibility criteria. Second, the investigator obtains the patient’s freely given, informed, and written consent. Finally, the investigator provides a copy of the informed consent form according to article L1122-1 of the Public Health Code. Patients who do not consent to the trial will be treated according to standard care. The “prematurity ROP group” will be defined as patients with infants developing ROP type 1 or 2 (visible on fundus examination after 4 weeks of life and at least 31 GA) and born before 29 GA. The “prematurity no-ROP group” will be defined as patients with infants without any stage of ROP and born before 29 GA. The “full-term no ROP group” will comprise patients with infants without ROP and born at full-term. Mother-infant dyads in life-threatening conditions will not be included (Table 1).

**Table 1 Tab1:** Inclusion and exclusion criteria

Inclusion criteria	Exclusion criteria
Mothers delivering a premature newborn of less than 29 weeks’ gestational age (GA) after obtaining their non-opposition	Mothers giving birth between 29 and 38 GA + 6 days
Mothers giving birth at full term between 39 and 41 GA + 6 days, after obtaining their non-opposition	Mothers with a vital prognosis
The mother must be of legal age	The mother is not affiliated with a social security system
The mother must not be under legal guardianship	For full-term mothers: Current or previous history of an obstetrical pathology of any origin (vascular such as gestational hypertension, pre-eclampsia; gestational diabetes; intrauterine growth retardation, maternal infection during pregnancy such as toxoplasmosis, cytomegalovirus, rubella, measles, chickenpox)

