### Sample size calculation

The sample size in this study was calculated using multiple regression to detect a difference of 3 in the mean plasma FA receptor level between groups with 80% power (α error = 0.05), a ratio of 2:1 between groups, and a coefficient of determination R^2^ of 0.10. Overall, a sample size of 100 mother-infant dyads is required: 70 mothers over 18 years of age giving birth before 29 GA and 30 mothers with full-term pregnancies (39–41 GA + 6 days).

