## Statistical methods

The data will be reviewed at the end of the study before statistical analysis. Statistical analysis will be performed using STATA v15.1 (StataCorp, College Station, TX, USA).

Quantitative data will be expressed as median and interquartile range [IQR]. The groups will be compared for quantitative variables using parametric or non-parametric tests according to normal/abnormal data distribution, and for qualitative variables using the chi-square test or Fisher’s exact test. Spearman correlations will be used to analyze the extent to which the placental FA receptor expression is associated with ROP occurrence. The extent to which the placental FA receptor expression is associated with the maternal blood FA level and the blood cord FA level will be analyzed through Spearman correlations. Linear regression analyses will be carried out to compare placental FA receptor expression levels as a function of GA. Statistical significance is to be set at *p* < 0.05, and the tests will be two-tailed.

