## Discussion

PUFAs from the omega-3 series are strong regulators of perinatal retinal vascular development. It is now well established that n-3 LC-PUFAs play crucial roles in retinal angiogenesis and vascularization [44], limit the severity of pathological retinal neovascularization, and improve the regression of ocular vascular lesions [45]. To our knowledge, there are limited data available on lipid or LC-PUFA status in preterm infants developing ROP. Nutrient transport across the placenta and into fetal circulation is complex. Like glucose or amino acids, FAs are an essential macronutrient for adequate fetal growth and they cross the syncytiotrophoblast through specific transporters [46]. FATPs and FAT CD36 are integral membrane proteins that are important for the uptake of LC-PUFA [47]. FATP1 and FATP4 are mostly studied in placental tissue as their expression is correlated with DHA levels in maternal plasma, cord blood, and placental phospholipids, suggesting an important role in the transfer of LC-PUFA [33]. All of the n-6 and n-3 FAs accumulated by the fetus must be derived from the mother via LC-PUFA placental transfer [48]. Therefore, the diet must provide this after birth [28]. Previously, Pallot and colleagues in the Omega-ROP study were the first to characterize erythrocyte lipids in preterm infants born before 29 weeks of gestational age (GA) and showed abnormalities in placental PUFA transfer in preterm infants who will develop ROP [32]. DHA levels in erythrocytes were shown to range between 5.5 and 5.8% of total FAs in mothers who delivered full-term infants (39–41 GA) [49] and were reported to be reduced to 2.5% of total FAs in mothers of 33 GA preterm infants [50].

We hypothesize that in utero bioavailability of n-6 and n-3 LC-PUFAs could influence the occurrence of ROP. Mechanistic studies are needed to determine whether dysfunction in the placental transfer of n-3 LC-PUFAs is involved in the maternal and fetal erythrocyte FA modifications observed. In the OmegaROP-2 study, we aim to evaluate the association between the expression level of placental FA receptors and the development of ROP.

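### As written, the fatty-acid/receptor correlations and the gestational-age regression have no term for group, so if all dyads enter, term status can confound the correlations and dominates the GA slope

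*Protocol article*

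**What the plan says.** All references are to the protocol article.

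- **Eligibility (Table 1).** Deliveries before 29 weeks are admitted, as are "Mothers giving birth at full term between 39 and 41 GA + 6 days". Excluded are "Mothers giving birth between 29 and 38 GA + 6 days". A further exclusion applies to one group only: "For full-term mothers: Current or previous history of an obstetrical pathology of any origin".
- **Size (Sample size calculation).** "70 mothers over 18 years of age giving birth before 29 GA and 30 mothers with full-term pregnancies".
- **Secondary outcomes 1 and 2 (Outcomes).** These are the relationships of cord blood and of maternal blood fatty-acid (FA) content with placental receptor expression. No group is specified.
- **Analysis (Statistical methods).** The extent to which expression is "associated with the maternal blood FA level and the blood cord FA level will be analyzed through Spearman correlations". Separately, "Linear regression analyses will be carried out to compare placental FA receptor expression levels as a function of GA". No stratum, covariate or analysis set is given for either.
- **Levels by group (Discussion).** Maternal erythrocyte DHA is put at 5.5 to 5.8% of total FAs for full-term deliveries and "reported to be reduced to 2.5% of total FAs in mothers of 33 GA preterm infants".
- **Levels by group (Background).** Infant erythrocyte omega-3 composition is described as roughly stable, with values cited from 24 to 33 GA. In the previous Omega-ROP study, mothers of newborns who developed ROP had DHA above the normal range.

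**The concern.** A plain Spearman coefficient has no place for a group term. When a sample consists of two clusters that differ in both variables, the coefficient over everyone picks up the distance between the clusters, whether or not the variables move together inside either one. Here the clusters are 10 weeks of gestation apart and were selected under different obstetric criteria. A correlation between DHA and receptor expression could therefore reflect only that term and preterm placentas and mothers differ. Shifts in opposite directions could instead hide a real association among the preterm dyads.

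The GA regression has a related problem. With nobody between 29+0 and 38+6 weeks, a straight line through all dyads joins two clusters. Its slope would read as an effect of gestation when it also carries term status and the obstetric-pathology exclusion. At stake are secondary outcomes 1 and 2 and the reading of the GA regression.

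**Working it through.** **The plan's own figure.** The stated 100 dyads come from multiple regression with R² = 0.10, so f² = 0.10/0.90, at 80% power and α = 0.05. The number of predictors is not given. A noncentral-F calculation gives N = 73, 90, 103 and 113 for 1, 2, 3 and 4 predictors, and power at N = 100 is 79.0% with three. The figure can be neither confirmed nor refuted, and it does not bear on this point. It does help to set a scale: at 70:30 the difference detectable with 80% power is (1.960 + 0.842) × √(1/70 + 1/30) = 2.802 × 0.218 = 0.61 SD. A 0.6 SD difference in expression is therefore not an extreme scenario.

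**GA regression.** Inputs: 70 and 30 dyads. Assumption: GA is uniform over 24–29 and over 39–42 weeks.

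- Group means are 26.5 and 40.5 weeks, 14 weeks apart. Between-group variance = 0.7 × 0.3 × 14² = 41.16.
- Within-group variance = 0.7 × 5²/12 + 0.3 × 3²/12 = 1.458 + 0.225 = 1.683.
- Between-group share = 41.16/(41.16 + 1.683) = 96%. Starting the preterm range at 23 or 25 weeks gives 95% or 97%.
- For least squares, pooled slope = w × (difference in group means/14) + (1 − w) × within-group slope, where w is this share. About 96% of the weight falls on the group contrast.

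Simulation (3,000 runs) with no GA effect inside either group:

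| Term shift in expression (SD) | Pooled GA slope significant | Power of plain two-group test |
|---|---|---|
| 0.3 | 27% | 28% |
| 0.61 | 78% | 80% |
| 0.73 | 90% | 92% |
| 1.0 | 99.5% | 99.6% |

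The two columns nearly coincide. A slope fitted in preterm dyads only was significant in about 5% of runs (checked at the 1.0 SD shift).

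**FA–receptor correlations.** Let the groups differ by dx SD in FA level and dy SD in expression, with zero correlation inside each group. The pooled product-moment correlation is

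0.21·dx·dy / √[(1 + 0.21·dx²)(1 + 0.21·dy²)], where 0.21 = 0.7 × 0.3.

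It is zero if either shift is zero. For dx = dy = 1 it is 0.21/1.21 = 0.17, and the simulated mean Spearman is also 0.17. Simulated share significant at two-sided 0.05 (3,000 runs, 70:30):

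| dx, dy (SD) | Mean rho | Pooled Spearman significant |
|---|---|---|
| 1, 0 or 0, 1 | 0.00 | about 5% |
| 0.3, 0.3 | 0.02 | 5.8% |
| 0.5, 0.5 | 0.05 | 7.3% |
| 0.73, 0.73 | 0.10 | 17% |
| 1, 1 | 0.17 | 40% |
| 1.5, 1.5 | 0.32 | 92% |
| 2, 0.61 | 0.18 | 42% |
| 3, 0.61 | 0.20 | 53% |
| 2, 1 | 0.28 | 80% |
| 3, 1 | 0.32 | 92% |

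Repeat runs put the 0.3 to 0.5 SD rows at about 6 to 8%. Ranking within group, or using preterm dyads only, keeps the rate at about 4 to 6% throughout.

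To place maternal DHA on this scale, take 5.65% (the midpoint at term) against 2.5%, a difference of 3.15 points. With an assumed SD of 1.0 to 1.5, dx = 3.15 to 2.1. The pooled false-positive rate is then about 45 to 52% if expression differs by 0.6 SD and 83 to 93% if by 1.0 SD.

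**Masking.** With a true within-group correlation of 0.30 and opposite shifts of 1 SD, the pooled correlation is about (0.30 − 0.21)/1.21 = 0.07 (simulated 0.06). Power is 10%, against 81% when stratified.

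**The case against.** The strongest reply is that pooling is nowhere stated. Statistical methods names techniques and not analysis sets, the design defines three groups, and a full protocol or analysis plan not shown may restrict or stratify. That stands, and it makes the point conditional. It does not dispose of it: the article names a specific method that cannot carry a group term and attaches no limit to it, so an analysis of all dyads is the plain reading.

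A reader might go further and infer that the correlations simply reproduce the term-versus-preterm difference. The documents do not support that, for four reasons.

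- Distortion needs both variables to differ by group, and no figure for receptor expression by group or by GA is given.
- The 2.5% maternal DHA value is from 33 GA, an age that the study excludes. It has no SD and a different cited source from the term values.
- The Omega-ROP finding of raised DHA in mothers of ROP infants points the other way for part of the preterm group.
- For cord blood there is no term value at all, and the Background values from 24 to 33 GA suggest stability.

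Two further readings also fail. A GA slope driven by the group contrast is not spurious: it reflects a real difference in expression and is only mislabelled if read as gestation. And the article does not say that this slope will adjust the preterm ROP comparison, or that a correlation will be taken as proof of mechanism. It speaks of relationships and says that mechanistic studies are needed.

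**Conclusion.** The point holds in conditional form. If all dyads enter, the GA slope is essentially the term-versus-preterm contrast and cannot separate gestation from term status or from the one-sided exclusion. This rests on the excluded 10 weeks and an assumed even spread of GA, and it changes little across the ranges tried (95 to 97%).

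The correlations can be confounded by term status, but by how much is unknown. The false-positive rate runs from its nominal 5% to above 90%, depending on two group shifts that the documents do not give. The case is better supported for maternal DHA than for cord FA. All SDs are assumed.

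The primary outcome is not touched by this point. It is a cheap change worth making before the end-of-study analysis.

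**What to change.** - Make the analysis of secondary outcomes 1 and 2 a Spearman correlation stratified by group (ranks taken within preterm and within term dyads), or a partial Spearman with a group indicator. Report the preterm-only correlations beside it.
- Fit the regression of expression on GA in preterm dyads only.
- Report term versus preterm expression as a separate two-group difference, labelled as also reflecting the obstetric-pathology exclusion applied to term mothers.
- State which dyads enter each analysis.

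No new data are needed. The cost is somewhat wider intervals. At a true rho of 0.30, the Fisher-z approximation with variance 1.06/(n − 3) gives power of 84% at n = 100 and 69% at n = 70; repeat runs put preterm-only at 67 to 69%. Stratifying all 100 dyads keeps about 81%.

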**Discussion:**

The results of this study will have a tangible impact on public health. Indeed, if we show a correlation between the expression level of placental omega-3 receptors and the occurrence of ROP, it would be an essential step in discovering novel pathophysiological mechanisms involved in this retinopathy.

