Since retinal lipid analysis in humans is inconceivable due to its invasive nature, biochemists use circulating biomarkers of retinal LC-PUFAs. The lipid composition of erythrocyte membranes is considered a more reliable reflection than plasma since lipids in red blood cells are less sensitive to external factors. The omega-3 LC-PUFA composition of erythrocyte membranes does not appear to vary significantly in healthy children during the last weeks of gestation (4.7 ± 1.3% of total fatty acids for DHA at 24 GA [29], 5.2 ± 0.7% at 29 GA [30], 4.6 ± 0.4% at 33 GA [31], and 4.1% with a CI = [1.71–4.86] at 29 GA [32]). DHA is essential for fetal development and cannot be synthesized by the fetus. During pregnancy, fatty acids (FAs) are transferred from the maternal blood to the fetal blood via the placenta and the umbilical cord. At the microvillous membrane of the placenta, lipoprotein lipase induces the catabolism of triglycerides from the maternal blood, followed by placental uptake of free FA products. LC-PUFAs cross the microvillous membrane, the syncytium, and the basement membrane to reach the fetal blood circulation. The transport of nutrients and solutes across the syncytiotrophoblast occurs through several passive and active processes, including flow-limited diffusion, transcellular diffusion, protein-mediated transfer, and endocytosis/exocytosis. Selective transport of long-chain fatty acids occurs via specific transporters called fatty acid-binding protein (FABP) and fatty acid-transporting protein (FATP). These proteins have a major role in the transport of Fas [33, 34]. FATP1 and FATP4 are frequently studied in placental tissue since their expression is correlated with DHA levels in maternal plasma, cord blood, and placental phospholipids, suggesting an essential role in the transfer of LC-PUFA [35]. Recent research is beginning to uncover the mechanisms of DHA transmembrane and intracellular transport in the placenta. It is suggested that maternal health and nutrition during pregnancy could be important in determining FA transport and binding protein expression and, thereby, essential FA delivery to the fetus. Further knowledge in this domain may be the first step in developing targeted interventions to help optimize fetal retinal growth and limit the incidence of ROP.

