## Objectives and statistical analysis

### Outcomes

The primary outcome is to evaluate the relationship between the expression level of placental FA receptors and ROP occurrence.

Secondary outcomes of the study are: (1) assessment of the relationship between blood cord FA content and the expression level of placental FA receptors; (2) assessment of the relationship between maternal blood FA content and the expression level of placental FA receptors; (3) assessment of the relationship between placental FA receptor expression levels and the occurrence and severity of ROP.

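### The primary outcome covers several placental receptors, but the plan applies an unadjusted p < 0.05 and sizes for one receptor level, with no lead receptor or correction stated

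*Protocol article*

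**What the plan says.** Five places in the protocol article bear on this point.

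- *Outcomes*: "The primary outcome is to evaluate the relationship between the expression level of placental FA receptors and ROP occurrence". The receptors are plural and none is singled out.
- *Placental lipid transport/receptor protein analyses*: the Western blots quantify proteins of interest, again plural. Neither their number nor their identity is given.
- *Statistical methods*, analysis: "Spearman correlations will be used to analyze the extent to which the placental FA receptor expression is associated with ROP occurrence".
- *Statistical methods*, error rate: "Statistical significance is to be set at" p < 0.05, two-tailed. This is the only statement on error control in the article.
- *Sample size calculation*: 100 dyads (70 preterm, 30 full-term) to detect a difference of 3 in one mean receptor level, with 80% power and alpha 0.05.

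The Discussion part of the Abstract describes success as follows: "if we show a correlation between the expression level of placental omega-3 receptors and the occurrence of ROP". It does not say which receptor must show the correlation, or whether all must.

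**The concern.** The primary question is plural, while both the error rate and the sample size are set for one test. With two or more receptors, each tested at 0.05, there is more than one chance of a false primary finding and nothing in the article holds the total at 5%. Nor does it give an order of testing or a combined score that would reduce the receptors to one primary test.

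At stake is how far a positive result can be trusted. The Abstract gives finding a new target for preventing ROP as an aim. If one receptor out of several reaches p < 0.05, a reader of the results could not tell from this article whether that receptor was chosen in advance or picked out afterwards.

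**Working it through.** **The plan's own figure.** The total of 100 cannot be reproduced, because the standard deviation and the number of predictors are not given.

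- Multiple regression with R² = 0.10 (f² = 0.10/0.90 = 0.111), 80% power and alpha 0.05 needs 73, 90, 103, 113 or 122 dyads for 1 to 5 predictors. Only three predictors comes close to 100, and that number is an assumption.
- A two-mean comparison with a difference of 3 and a 2:1 ratio gives 100 if the SD is about 5.05, which is also an assumption.

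On either reading the calculation uses one alpha of 0.05 for one receptor level. It makes no allowance for several receptors.

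**Inputs for the error rate.** The per-test alpha is 0.05 two-sided (*Statistical methods*). The number of receptors k is not stated, so k = 2 to 4 is assumed. The correlation between the receptors' test statistics is not stated either, so it is varied from 0 to 0.9.

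**Independent tests.** The chance of at least one false positive is 1 − (1 − 0.05)^k:

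- k = 2: 1 − 0.95² = 0.0975
- k = 3: 1 − 0.95³ = 0.143
- k = 4: 1 − 0.95⁴ = 0.185

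**Correlated tests.** These come from simulating k equally correlated two-sided z-tests (400,000 draws) with no true association.

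| Receptors | Independent | Correlation 0.5 | Correlation 0.8 | Correlation 0.9 |
|---|---|---|---|---|
| 2 | 9.75% | 9.1% | 7.8% | 7.1% |
| 3 | 14.3% | 12.6% | 9.8% | 8.3% |
| 4 | 18.5% | 15.6% | 11.4% | 9.3% |

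Every cell is above 5%. The table counts one test per receptor. *Statistical methods* also provides for group comparisons of quantitative variables. If these were applied to receptor expression as well, they would be further tests on the same data; they are not counted here.

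**Effect of a correction.** Holm tests the smallest p-value at 0.05/k, which is 0.025, 0.0167 or 0.0125 for k = 2, 3 or 4. If every test used that level (Bonferroni), the family-wise error under independence would be 1 − (1 − 0.05/k)^k, about 4.9% in each case. For power, assume that R² = 0.10 is the effect of a single receptor and that all 100 dyads enter the test; the article states neither. Power is then 91.0% at alpha 0.05, and 85.3%, 81.3% and 78.3% at the three stricter levels. The total needed for 80% power is 89, 98 and 104. Holm is never less powerful than Bonferroni, so these are its least favourable figures.

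**The case against.** The strongest reply is that this is a condensed article. The antibody panel, the order of testing and any multiplicity rule may stand in a full protocol or analysis plan that is not shown. The article does not say that no adjustment will be made, and a nominal 0.05 is compatible with Holm or a lead receptor elsewhere. It also refers to receptor expression in the singular under *Statistical methods*, so a single summary measure is not excluded.

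Part of this stands. Separate testing of each receptor is an inference, and it cannot be claimed that no correction exists anywhere. But the point does not rest on silence alone. The article itself sets a plural primary outcome beside one flat threshold and a sample size for one receptor level, and these do not fit together. It describes no summary measure.

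The reply is also right about several stronger readings that a reader might infer:

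- **A panel of four receptors, and so a rate of 18.5%.** Background and Discussion mention FABP, FATP1, FATP4 and FAT CD36, for example "FATPs and FAT CD36 are integral membrane proteins that are important for the uptake of LC-PUFA". These are candidates from the literature, not an assay list, and FABP and FATP are family names. The 18.5% also needs independence, whereas related transporters measured in the same placentas may well be correlated.
- **A large count of false positives among the secondary correlations.** The article does not say how many fatty acids will be tested. Assuming that every such association is null would also conflict with the Background, which reports FATP1 and FATP4 expression to be correlated with DHA levels.
- **Few ROP cases making the problem worse.** The number of cases limits power and precision; it does not raise the type I error rate.
- **Secondary outcome 3 adding to the error because it names ROP occurrence again.** Repeating the same test on the same data is redundant wording and adds no new chance of error.

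**Conclusion.** The point holds in limited form. As written, the plan does not keep the primary false-positive rate at 5% if two or more receptors are each tested against ROP. The excess is modest for two receptors (about 7% to 10%) and larger for four (about 9% to 18.5%). These figures rest on three assumptions: two to four receptors, separate tests, and correlations between 0 and 0.9. The direction does not depend on the exact count. Only a single primary receptor, a single summary measure or a correction would remove the excess, and the article states none of these.

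**What to change.** Inclusion is still under way according to *Trial status*. Before any blot is linked to ROP status, adopt one of two rules and record it in the protocol:

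1. Name one lead receptor for the primary test at two-sided 0.05. The article gives most attention to FATP1 and FATP4; the choice is the sponsor's.
2. List the primary receptors and apply Holm at a family-wise 5%.

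Under either rule, label the remaining receptor and receptor-by-fatty-acid correlations exploratory. If an unseen analysis plan already contains such a rule, one sentence bringing the article's wording into line is enough.

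The change affects wording and analysis only, not data collection. The first rule costs the lead receptor no power, but the others can no longer support a primary claim. The second sets a stricter threshold, and so gives slightly lower power for each receptor.
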